#### Outcome measures

Our primary outcome measure is the number of women screened and the proportion of screen-positive women successfully undergoing treatment. Secondary outcomes measures will include other implementation outcomes (see Specific Objective 3 below), and if successful, will be utilized to inform future research to take this approach to scale across Mozambique.

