### Aims/objectives

The overall aim of this study is to evaluate implementation best practices for deploying a *Screen-Triage-Treat* approach to cervical cancer screening utilizing self-collected HPV DNA testing among HIV-infected women in care within select health facilities in Chókwè District, Mozambique. The main objectives of this study are:To develop an in-depth understanding of the HPV *Screen-Triage-Treat* care cascade within the HIV care and treatment services based on a collaborative, exploration-focused process with local stakeholders.To evaluate the effectiveness of the *Screen-Triage-Treat* approach to cervical cancer screening utilizing self-collected HPV DNA testing.To use the Consolidated Framework for Implementation Research (CFIR) to identify factors that explain site-level and provider-level variation in the implementation of the *Screen-Triage-Treat* approach to cervical cancer screening utilizing self-collected HPV DNA testing.

Table 1 shows the SPIRIT diagram including the schedule of enrollment, intervention, and assessment.

**Table 1 Tab1:** SPIRIT diagram: schedule of enrollment, intervention, and assessment

Study Period	Pre-Implementation Phase	Implementation Phase	Follow-up Phase	Post-implementation Evaluation
Timepoint	Month −2 to 0	Month 0–30	Month 1–30	Month 31–33
Enrollment:				
Site preparation and staff training	X			
Two-week pilot assessment period	X			
Model participant enrollment (1–2/day)		X		
Participant eligibility screening		X		
Informed Consent		X		
Intervention:				
Self-collected HPV DNA testing (Screen)		X		
HPV result reporting (same-day CHC; weekly in periphery)		X		
VIA and thermal ablation if eligible (Triage-and-treat)		X		
Referral to higher level of care for LEEP/colposcopy in not eligible for ablation		X		
Assessments:				
Baseline retrospective data (past 12 months)	X			
Process mapping/group model building workshop and qualitative interviews (Objective 1a-c)	X	X		
Quantitative data collection (HPV, VIA, treatment rates)		X		
Implementation Outcomes (adoption, fidelity, reach, acceptability)		X	X	
Qualitative provider interviews (CFIR domain)			X	
Statistical analysis of primary outcome (proportion of HPV + women treated, Objective 2)			X	
Analysis of secondary outcomes (implementation outcomes, Objective 3)			X	
Dissemination workshops and final reporting				X

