#### Visual Assessment for Treatment (VAT)

Women with a positive HPV test will undergo visual assessment for treatment (VAT) followed by ablation using thermal ablation, if eligible (Fig. 3). Women with lesions not eligible for ablation will be referred to the neighboring Hospital Rural of Chókwè for LEEP or other treatment, as appropriate. During the examination, the health care provider will also use a smart phone device to take images/videos of the cervix so that he or she will be able to document the test results and perform quality control. Participants will be asked if they agree with having their images/videos used for future research. If they agree, a future use research informed consent document for the photo will be reviewed and signed. Images/videos collected to be used for future research will be de-identified.

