**Fig. 3 Fig3:**
[figure not shown]
Flow diagram for HPV DNA testing in Women Living with HIV. *HPV = Human papillomavirus; VIA = Visual Inspection with Acetic Acid; TA = Thermal ablation; and LEEP = Loop Electrosurgical Excision Procedure

Following assessment as described above, women who screen positive will be eligible for ablative therapy if there is no suspicion of invasive or glandular disease, and if:The transformation zone (TZ) is fully visible, the whole lesion is visible, and it does not extend into the endocervix; orThe lesion is type 1 TZ (when it only contains ectocervical components); orThe lesion is type 2 TZ where the probe tip will achieve complete ablation of the squamocolumnar junction (SCJ) epithelium, i.e., where it can reach the upper limit of the TZ. Sometimes the SCJ can be seen high in the canal, but a probe tip would not reach it.

Women are not eligible for ablative therapy if there is any suspicion of invasive or glandular disease (i.e., adenocarcinoma or adenocarcinoma in situ), and:The TZ is not fully visible because it is endocervical (Type 3 TZ), orIt is a type 2 TZ where the SCJ is out of reach of the probe tip.The lesion(s) cover > 75% of the cervix.

If the above criteria for ablation are not met, the woman will be referred to a gynecologist at the closest facility (Hospital Rural of Chókwè). The clinician will evaluate the patient with colposcopy, cervical biopsy, endocervical curettage, and/or immediate LEEP as appropriate per standard guidelines. Women diagnosed with invasive cervical cancer or requiring further diagnostic workup not feasible in this facility will be referred to either Xai-Xai Provincial Hospital (HPX) or Maputo Central Hospital (HCM).

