#### Date collection

Prior to intervention roll-out, baseline data will be retrospectively collected for the prior 12 months at each of the selected study sites, including the number of women accessing care for HIV care and treatment services each month; the number of women screened for cervical cancer through standard of care protocols; the proportion of screen-positive women who then received treatment or referral for treatment, and the length of time between screening positive and receiving treatment, if appropriate. Data will be collected by study team members (physician, nurse, or medical technicians) utilizing a paper-based instrument and then uploaded into a password-protected, tablet-based, online research data capture (REDCap) database. This method allows for the recording of demographic information, medical and medication history, and any pertinent laboratory test results. Data quality control will be conducted by study investigators who will review all completed paper-based study instruments and confirm the accuracy of data entered into REDCap.

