#### Sample size and power calculations

We used our primary outcome, more specifically, the proportion of HPV screen positive women that will successfully undergo treatment, to power the study. We used preliminary data to estimate a sample size sufficient to detect, with 90% power, an improvement of at least 15% in the proportion of women undergoing treatment compared to the current standard of practice. CHC currently sees approximately 1,200 HIV adult outpatient visits per month, of which 52% are female (*n* = 624) and approximately 75% of women are between the ages of 25–49 years (*n* = 468). Of these, we conservatively expect approximately 60% will not have been screened in the last three years and meet screening eligibility (*n* = 280). Based on preliminary data, the prevalence of HPV-positivity among WLWH was estimated to be approximately 40%; however, in our calculations, we again took a more conservative approach and assumed an HPV prevalence of 35% (*n* = 98). Under the current standard of care scenario we estimate that approximately 36% of HPV screen positive women go on to receive treatment (CHC currently performs, on average, 35 thermal ablation procedures per month). Figure 4 below shows statistical power curves to detect improvements, through utilization of the HPV self-testing *Screen-Triage-Treat* approach, varying from 10 to 20% in the proportion of HPV-screen positive women undergoing same day thermal ablation, compared to standard of care. We used a type-I error fixed at 5%, two-sample, two-sided binomial test, and assumed trimestral cumulative data to plot the curves, for different prevalences of HPV. Calculations were performed using the R software (*pwr* R package) [28]. Based on Fig. 4, we will be able to detect over 15% improvements in the proportion of HPV-screen positive women undergoing same day thermal ablation compared to standard of care, while assuming a prevalence of 35% or even lower at 25%, with at least 90% power.

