#### Statistical analysis plan

Using data captured during implementation of the *Screen-Triage-Treat* approach for cervical cancer screening, we will evaluate intervention fidelity as a function of 1) *Completion Rate*: the proportion of enrolled women who turned in a self-collected sample for HPV DNA testing; 2) *Test Result Notification Rate*: the proportion of women who were notified of their HPV DNA test result on the same day as sample collection; and 3) *Treatment Rate*: the proportion of screen-positive women who were treated with thermal ablation, if appropriate, or referral for higher level of care.

Patients’ characteristics and clinical values will be summarized in tables and figures. Continuous variables will be presented as medians and interquartile ranges. Categorical variables as frequencies and percentages. Descriptive statistics will be done for the overall population and stratified intervention status and study site. Continuous variables will be compared via the Mann–Whitney-Wilcoxon test, and categorical variables will be compared via the chi-square test. We will use a generalized linear model (GLM) with the logit link to and perform an interrupted time series to assess the impact of the intervention and the proportion of patients who subsequently underwent treatment for cervical cancer. The model will regress the outcome on intervention status (binary variables, yes/no), calendar time (in months), and an interaction between the two terms. By doing this we will be able to assess the immediate impact of the intervention (also known as level change) as well as its effect over time (sustained effect of the intervention) compared to the counterfactual scenario of no intervention being implemented. Analysis and comparisons will be performed overall, combining all sites, as well as being stratified by health facilities. We will adjust for relevant demographic and clinical characteristics, such as age, CD4 count, and viral load, among other factors. Continuous variables will be modeled via restricted cubic splines. We will again use GLM with a gaussian link to estimate the impact of the intervention on the number of WLWH diagnosed with HPV, adjusting for the same covariates as above, and following the same steps as above (e.g., another interrupted time series). If the normality assumption is violated, we plan to use ordinal regression models as an alternative. We do not expect issues with statistical over-fitting.

### Specific objective 3

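### The primary treated proportion has no consistent place for screen-positive women who are referred, fully evaluated and found to need no treatment, and the protocol scores them differently from section to section

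*Protocol article*

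**What the plan says.** The primary outcome (Specific objective 2, Outcome measures) is "the number of women screened and the proportion of screen-positive women successfully undergoing treatment". Table 1 repeats the proportion as "Statistical analysis of primary outcome (proportion of HPV + women treated, Objective 2". In both, every screen-positive woman is in the denominator and only treated women are in the numerator.

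The section on Visual Assessment for Treatment describes two routes. On the first, "Women with a positive HPV test will undergo visual assessment for treatment (VAT) followed by ablation using thermal ablation, if eligible". On the second, women outside the ablation criteria are referred to a gynecologist. One listed ground for ineligibility is "The TZ is not fully visible because it is endocervical (Type 3 TZ". At the referral hospital treatment is conditional: "The clinician will evaluate the patient with colposcopy, cervical biopsy, endocervical curettage, and/or immediate LEEP as appropriate per standard guidelines".

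Three other places use a different numerator:

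- Baseline data, collected for the 12 months before roll-out (Date collection): "the proportion of screen-positive women who then received treatment or referral for treatment".
- Treatment Rate, a fidelity measure (Statistical analysis plan): "the proportion of screen-positive women who were treated with thermal ablation, if appropriate, or referral for higher level of care".
- Power curves (Sample size and power calculations): improvements "varying from 10 to 20% in the proportion of HPV-screen positive women undergoing same day thermal ablation".

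**The concern.** The referral route can end properly with no treatment. A woman who attends, is examined and is found to need nothing has completed the cascade as the protocol describes it. The literal primary outcome nevertheless records her as not treated, in the same cell as a woman who never attended. Complete referral data would not cure this, because the outcome has no category for her.

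Two comparisons depend on the definition. One is the interrupted time series before and after roll-out, where the numerator listed for the baseline period (treated or referred) is not the primary numerator (treated). The other is the comparison by health facility. On the literal reading, a facility with more women outside the ablation criteria scores lower for reasons of case mix. If referral counts as success, it gains credit for women who may never have been seen.

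**Working it through.** **Scoring of the same woman under each definition**

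| Woman (screen-positive) | Outcome measures, Table 1 | Power curves | Baseline data | Treatment Rate |
|---|---|---|---|---|
| Thermal ablation, same day | success | success | success | success |
| Referred, treated | success | not | success | success |
| Referred, evaluated, needs no treatment | not | not | success | success |
| Referred, never attends | not | not | success | success |

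No column separates the last two rows.

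**The protocol's own figures, reproduced**

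- Baseline rate: 280 × 0.35 = 98 HPV-positive women per month, and 35/98 = 0.357, stated as 36%.
- Added treated women: 0.15 × 2,940 = 441.
- Power for 0.36 against 0.51, two-sided 5%, three months of data per period (98 × 3 = 294), arcsine method: 0.958, consistent with the stated 90% or more.

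**Effect of the literal reading (illustration)**

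Let u0 and u1 be the shares of screen-positive women, before and after roll-out, who are evaluated and need no treatment. The documents give neither, so the values below are assumptions. Take 0.36 and 0.51 as the true rates among women who need treatment.

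Literal difference = 0.51 × (1 − u1) − 0.36 × (1 − u0)

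Error = 0.36 × u0 − 0.51 × u1

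| u0 | u1 | Literal difference | Error, points | Power at 294 per period |
|---|---|---|---|---|
| 0 | 0 | 0.510 − 0.360 = 0.150 | 0 | 0.958 |
| 0 | 5% | 0.4845 − 0.360 = 0.1245 (about 12.4 points) | −2.55 | 0.865 |
| 0 | 10% | 0.459 − 0.360 = 0.099 | −5.1 | 0.686 |
| 5% | 0 | 0.510 − 0.342 = 0.168 | +1.8 | 0.985 |
| 5% | 5% | 0.4845 − 0.342 = 0.1425 | −0.75 | 0.941 |
| 5% | 10% | 0.459 − 0.342 = 0.117 | −3.3 | 0.827 |

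This component is downward whenever 0.51 × u1 exceeds 0.36 × u0, which includes every case where the share rises.

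**If referral counts as success**

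Women who need no treatment are then no longer failures, but women who never attend become successes. With an assumed 10% referred and half never attending, 0.10 × 0.5 = 5 points are false successes.

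**Why the share might rise**

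The Background gives VIA as the existing screening test, so a positive screen is a visual finding. Under the intervention HPV positivity is enough, and a type 3 transformation zone is a listed ground for ineligibility that names no lesion. A rise is therefore plausible, but no section states or quantifies it.

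**The case against.** The strongest objection is that the literal reading is only one of several. The baseline item and the Treatment Rate credit referral, and a condensed article may leave the operational meaning of successful treatment to the full protocol or analysis plan. The Treatment Rate is also a fidelity measure, so it may legitimately differ from the primary outcome. It stands that the literal reading cannot be taken as settled. The disagreement remains all the same: this article states the outcome, the baseline item and the powered quantity with three different numerators.

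The mechanism is also open. One referral sentence concerns women with lesions not eligible for ablation, while a later one refers anyone who does not meet the criteria. The ineligibility list joins suspected invasive or glandular disease to the transformation-zone conditions with an 'and'. Table 1 names VIA where the text describes visual assessment for treatment, and the flow diagram is not shown. How lesion-free HPV-positive women are routed cannot be settled here, and those statements must be reconciled.

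A reader might infer that the effect is, on balance, biased against the intervention. The documents do not support that:

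- The Background shows that VIA-era women were also referred, so the group can exist at baseline.
- The sentence on ablation of eligible HPV-positive women requires no lesion, which can raise the intervention numerator.
- Counting referral as success reverses the error.
- The planned 36% uses an HPV-positive denominator, whereas the collected baseline will use women positive under standard of care. If 280 women a month were screened with an assumed VIA-positive rate of 15% to 30%, 35 ablations would be 35/42 = 83% to 35/84 = 42%. That change could outweigh the mechanism described here.

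A reader might also set a large assumed share of mis-scored women directly against the planned 15-point gain. A share within one period and a difference between periods are not like quantities. Even 18% against 0% costs 0.51 × 0.18 = 9.2 points, less than 15.

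Finally, a ceiling below 100% is no error in itself, since the planned change is from 36% to 51%.

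**Conclusion.** The point holds as a defect of definition. Read literally, the primary proportion cannot tell correctly completed management without treatment from loss to follow-up, and the protocol's other numerators score the same women differently. The before-after and facility comparisons can be distorted as a result.

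Neither the size nor the net direction can be determined from the documents. They give no referral share, no share needing no treatment and no VIA-positive rate. The differences of 12.4 and 9.9 points are illustrations. They rest on true rates of 36% and 51%, no such women at baseline, and an assumed 5% or 10% in the intervention period. The outcome definition should be corrected; the plan's arithmetic is not in question.

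**What to change.** Use one numerator for the primary proportion, worded identically for both periods: management completed. This means treated (ablation, LEEP or other), or specialist evaluation completed with a documented finding that no treatment is indicated. Referral alone does not count. Report treated as a separate component, so that the treatment endpoint remains visible. Bring the baseline item and the power text into line with this numerator, and say plainly that the Treatment Rate is a separate fidelity measure.

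Where retrospective records do not show the result of a referral, give bounds: count all such women as completed, then all as not completed.

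The cost is one outcome definition, one added category on the case report form and the baseline tool, and the bounds analysis. The downside is reliance on the referral hospital's results and a slightly broader outcome. Those results are needed in any case to know which referred women were treated. Care does not change.

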#### Sample size and power calculations

We used our primary outcome, more specifically, the proportion of HPV screen positive women that will successfully undergo treatment, to power the study. We used preliminary data to estimate a sample size sufficient to detect, with 90% power, an improvement of at least 15% in the proportion of women undergoing treatment compared to the current standard of practice. CHC currently sees approximately 1,200 HIV adult outpatient visits per month, of which 52% are female (*n* = 624) and approximately 75% of women are between the ages of 25–49 years (*n* = 468). Of these, we conservatively expect approximately 60% will not have been screened in the last three years and meet screening eligibility (*n* = 280). Based on preliminary data, the prevalence of HPV-positivity among WLWH was estimated to be approximately 40%; however, in our calculations, we again took a more conservative approach and assumed an HPV prevalence of 35% (*n* = 98). Under the current standard of care scenario we estimate that approximately 36% of HPV screen positive women go on to receive treatment (CHC currently performs, on average, 35 thermal ablation procedures per month). Figure 4 below shows statistical power curves to detect improvements, through utilization of the HPV self-testing *Screen-Triage-Treat* approach, varying from 10 to 20% in the proportion of HPV-screen positive women undergoing same day thermal ablation, compared to standard of care. We used a type-I error fixed at 5%, two-sample, two-sided binomial test, and assumed trimestral cumulative data to plot the curves, for different prevalences of HPV. Calculations were performed using the R software (*pwr* R package) [28]. Based on Fig. 4, we will be able to detect over 15% improvements in the proportion of HPV-screen positive women undergoing same day thermal ablation compared to standard of care, while assuming a prevalence of 35% or even lower at 25%, with at least 90% power.

**Fig. 4 Fig4:**
[figure not shown]
Power calculations

Thus, by screening at least 280 HIV-infected women per month for a total of 30 months (total *n* = 8,400, of which 35% are expected to be HPV-screen positive), we expect to have at least 441 (15% of 2,940) added HPV-screen positive women who will subsequently undergo treatment, compared to standard of care alone. Of the 8,400 women screened, we anticipate that roughly 6,900 will be screened at CHC and roughly 500 will come from each of the three peripheral health facilities.

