#### Study participants and enrollment period

Women accessing health care for HIV care and treatment services at CHC, between the ages of 25–49 years of age will be approached for enrollment into the study and subsequent cervical cancer screening. Following the “Model” Participant period, enrollment of participants will continue for a total of 30 months (Table 2).

**Table 2 Tab2:** Inclusion and Exclusion criteria

Inclusion Criteria	Exclusion Criteria
Women 25–49 years, accessing HIV care and treatment services	Physical or mental impairment that inhibits participation in the study
Not being pregnant	Pregnant women or < 6 weeks post-partum
Patients with a cervix (women who have undergone a total hysterectomy with removal of the cervix are not eligible)	

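### The 8,400-woman projection treats monthly clinic visits as new women for 30 months, so 8,400, 2,940 and 441 are upper-end figures that the stated volume does not support

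*Protocol article*

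**What the plan says.** The section Sample size and power calculations builds a monthly cascade for one site:

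- The starting point is a visit count: "CHC currently sees approximately 1,200 HIV adult outpatient visits per month, of which 52% are female", giving 624.
- Next, "approximately 75% of women are between the ages of 25–49 years", giving 468.
- Then "we conservatively expect approximately 60% will not have been screened in the last three years and meet screening eligibility", giving 280.
- An assumed HPV prevalence of 35% gives 98 positives a month.

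The paragraph after Fig. 4 scales this up "by screening at least 280 HIV-infected women per month for a total of 30 months". It arrives at 8,400 women, 2,940 HPV-positive (35%) and 441 additional women treated (15% of 2,940). It then divides the same 8,400 by site: "we anticipate that roughly 6,900 will be screened at CHC", with about 500 from each of three peripheral facilities.

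Table 2 states the main inclusion criterion as "Women 25–49 years, accessing HIV care and treatment services". It lists no criterion on screening history. Outcome measures names the number of women screened as part of the primary outcome.

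**The concern.** The unit changes between the two paragraphs. The cascade counts visits, the projection counts women, and no step converts one to the other. Two features of the plan make the difference matter. Patients in HIV care attend repeatedly, so one month's visitors overlap with the next month's. The 60% filter also looks back three years while enrolment lasts 30 months, so a woman screened in month 1 cannot be part of the 280 in any later month. The monthly figure therefore draws on a pool that is used up, apart from women newly due or newly in care.

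The derivation also lets every eligible woman accept and complete screening. Yet the plan counts acceptances in the model-participant period and reports a completion rate.

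At stake are the recruitment target, the expected number of positives and the projected benefit of 441. The interrupted time series also estimates a sustained effect over calendar months. If the pool shrinks, later months carry fewer positive women than a constant 98.

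**Working it through.** **1. The plan's own figures reproduce.** 1,200 × 0.52 = 624; × 0.75 = 468; × 0.60 = 280.8 per month. Then 280 × 30 = 8,400; × 0.35 = 2,940; × 0.15 = 441. Without rounding to 280 the totals are 8,424, 2,948 and 442. The multiplication is sound; the unit is not.

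**2. Visit gap that the CHC target implies.** Suppose patients attend on average every *m* months, at the same frequency across sex, age and screening history (assumption). The distinct women aged 25–49 in care at CHC then number 468 × *m*.

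- Unscreened at the start, each counted once: 0.60 × 468 × *m* = 280.8 × *m*.
- If the other 40% come due evenly over three years (assumption), the share available within 30 months is 0.60 + 0.40 × 30/36 = 0.933, giving 436.8 × *m*.
- For 6,900 with no turnover: 6,900/280.8 = 24.6 months, or 6,900/436.8 = 15.8 months.
- Under Table 2 as written, without the 60% filter: 6,900/468 = 14.7 months.

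**3. Distinct women at CHC at assumed intervals** (*m* is not in the document; full uptake, no turnover):

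| *m* (months) | 280.8 × *m* | 436.8 × *m* |
|---|---|---|
| 3 | 842 | 1,310 |
| 6 | 1,685 | 2,621 |
| 12 | 3,370 | 5,242 |

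The plan assigns 6,900 to CHC.

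**4. Adding new entrants.** Let a fraction *t* of the cohort enter care each year, all of them eligible (assumption). Women available over 2.5 years are (436.8 + 468 × 2.5 × *t*) × *m*.

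- *m* = 3: 1,661 at *t* = 10%, 2,363 at 30%.
- *m* = 6: 3,323 at 10%, 4,727 at 30%.
- *m* = 12: 6,646 at 10%, 8,050 at 20%, 9,454 at 30%. The 6,900 is reached at *t* = (6,900 − 5,242)/(5,616 × 2.5) = 11.8% a year.

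**5. Like-for-like effect on 441.** Take the 1,500 peripheral women as given and add the range in step 3. Total women are 2,342–2,810 (*m* = 3), 3,185–4,121 (*m* = 6) or 4,870–6,742 (*m* = 12), against 8,400. Multiplying by 0.35 × 0.15 gives 123–148, 167–216 or 256–354 added treatments, against 441. New entrants would raise these.

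**6. Site split.** 280 × 30 = 8,400 is already the whole total, from CHC visits alone. The split needs 6,900/30 = 230 a month at CHC and 1,500/30 = 50 a month elsewhere. No peripheral volume is given. If CHC did supply 280 a month and the others 50, the total would be 8,400 + 1,500 = 9,900.

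**7. Power.** For 36% versus 51%, two-sided 5% and 90% power, the normal approximation for two proportions gives 228 positives per group; the arcsine form gives 227.7. One quarter at 35% prevalence supplies 280 × 3 × 0.35 = 294 positives and 95.8% power. At 25% prevalence one quarter supplies 210 and 87.6%, two quarters 420 and 99.3%. Even at three-monthly visits, CHC alone has 842 × 0.35 = 295 positives at full uptake.

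**The case against.** The strongest reply is that the article never states how many distinct patients CHC has, how often they attend or how many enter care each year. No shortfall can then be proved. That stands: step 4 shows that yearly visits with about 12% new entrants a year reach 6,900 at full uptake. It does not supply the missing conversion, and at 3- or 6-monthly visits the target is missed even with 30% entering each year.

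Second, not every visit is counted. The filters leave 280 of 1,200, or 23%. This is correct, but the filters select which visits count and do not remove repeats of the same woman.

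Third, the CHC plan of 230 a month is 82% of the 280 derived there (230/280.8), so it could be read as deliberate caution. It does mean that the CHC target would not need full uptake of the monthly 280. The article does not present the gap as a refusal allowance, however, and it still obtains 8,400 as 280 × 30 before splitting it.

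Fourth, a reader might infer that the target can be met only by enrolling the same women again, which would make observations dependent. The article does not say this. Nothing in it permits re-enrolment, the case report form records earlier screening results, and an explicit bar is detail that an article commonly leaves to the full protocol.

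**Conclusion.** The concern holds as a fault in how the projection is derived. A visit count is relabelled as women and multiplied by 30, with no allowance for repeat attendance, for women already screened or for refusal. The figures 8,400, 2,940 and 441 are therefore upper-end, visit-based numbers that the stated clinic volume does not support. The site split also does not follow from the CHC-only derivation, and that inconsistency needs no assumption.

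The size of any shortfall depends on visit interval and turnover, which the document does not give. Two stronger conclusions are tempting and should not be drawn. The first is that 8,400 is impossible or overstated several-fold: that follows at short intervals but not at yearly visits with moderate turnover. The second is that the study is underpowered. The power curves rest on cumulative quarterly data, not on 8,400, and the 90% statement largely stands. It would be in doubt only at very short intervals (monthly visits leave about 98 unscreened-pool positives at CHC), and it dips to 87.6% if a single quarter at 25% prevalence is used.

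**What to change.** Rederive 8,400, 2,940, 441 and the site split, facility by facility, as follows: unique women aged 25–49 in HIV care (from the register), times the share unscreened in three years, times expected uptake, plus women newly due or newly in care over 30 months. State the visit interval and turnover used, and give the volumes of the three peripheral facilities.

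Reconcile Table 2 with the screening-history filter in the sample-size section, so that the population projected is the population enrolled. State that each woman counts once in the number of women screened.

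The cost is a set of register counts and an amended sample-size paragraph and Table 2. The stated totals will probably look less favourable. No extra patients are needed, and the power paragraph can largely remain.
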